**Physiologic measures**				
Height	x			
Weight	x	x	x	x
Body mass index (BMI)	x	x	x	x
Waist circumference	x	x	x	x
Blood pressure	x	x	x	x
**Laboratory measures**				
Fasting insulin	x	x	x	x
Fasting plasma glucose	x	x	x	x
Fasting triglycerides	x	x	x	x
Fasting cholesterol (total, HDL, LDL)	x	x	x	x
**Self-reported measures**				
Age	x			
Gender	x			
Race	x			
Ethnicity	x			
Education level	x	x	x	x
Medicaid status	x	x	x	x
Medicare disability status	x	x	x	x
Marital status	x	x	x	x
Employment status	x	x	x	x
Annual and monthly income	x	x	x	x
Number of individuals supported by income	x	x	x	x
Income source	x	x	x	x
SF-36 general health subscale [47-49]	x	x	x	x
Behavior and Symptom Identification Scale (BASIS-24) [50]	x	x	x	x
Colorado Symptom Index (CSI) [51,52]	x	x	x	x
Self-reported medications^1^	x	x	x	x
Wisconsin Quality of Life Index (W-QLI) [53-55]	x	x	x	x
Patient Activation Measure (PAM) [56]	x	x	x	x
Body Weight, Image and Self-Esteem Evaluation Questionnaire (B-WISE) [57]	x	x	x	x
Social support scales for eating and exercise behavior [58]	x	x	x	x
Exercise confidence questionnaire [59]	x	x	x	x
Eating habits confidence questionnaire [59]	x	x	x	x
Weight outcome expectancies- ideal and goal weight [60,61]	x	x	x	x
7-day physical activity and sleep log [27]	x	x	x	x
7-day fruit and vegetable consumption [62]	x	x	x	x
Self-reported other efforts to lose weight	x	x	x	x

^1^Self-reported medications were also collected at 18 months.

### Data analysis

#### Effectiveness analyses of primary aims

We will use generalized estimating equations (GEE) [63] to test the effectiveness of the intervention. GEE estimates the population averaged model while accounting for the correlation among observations as a result of having multiple measures from the same person over time. The primary coefficient of interest will be the time by group (control vs. intervention) interaction, which will indicate the degree of differential change across time between the control and intervention groups. We will include age and study site and time-invariant covariates. Use of outcomes-related medications will be included as time-varying covariates (e.g., controlling for metformin usage when testing intervention efficacy on diabetes risk). The GEE models will be based on the normal distribution with identity link, and the working covariance matrix will be specified as exchangeable. An advantage of GEE is that it is able to estimate models when data are incomplete, assuming the data are missing at random and the working covariance matrix is correctly specified [63]. This will allow us to include all participants according to their initial group assignment in the analyses, which is consistent with the intent-to-treat principle.

For every outcome, we will conduct a series of sensitivity analyses by using transformations that improve the normality of the outcome, using a different family and link (e.g., negative binomial with log link) where appropriate, and using an unstructured working covariance matrix.

Finally, we will also examine between-group differences for various conceptualizations for the primary outcome of weight, including percentage weight change, the proportion of participants who are at or below his or her baseline weight, and the proportion of participants who lose at least 5% and 10% of their baseline weight. These will be computed at all follow-up timepoints. These are not intent-to-treat results, as these computations require that data are not missing in order to compute the necessary change scores for deriving these different measures of weight. We will test the difference in percentage weight change between the intervention and control groups using a one-way ANCOVA, and test whether the proportion of participants who are at or below their baseline weight at follow-up is different between the arms using multiple logistic regression. We will include age, site, and medications that are known to affect weight as covariates in all analyses.

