At the second screening visit, participants arrived having fasted for at least eight hours, had their blood drawn and their blood pressure and waist circumference measured. Individuals who had not been fasting were rescheduled. All individuals received reminder post-cards prior to the visit that included fasting and medication instructions (i.e., directions to postpone taking diabetes medications until after the fasting blood draw) and asking them to wear loose clothing to aid measurements. Participants also received reminder telephone calls the day before the visit. Following the blood draw, participants were provided with a snack and asked to take any medications at that time if they could not do so prior to the blood draw. They were then randomized to either intervention or usual care groups using a blocked, stratified procedure to ensure that group assignments remained balanced across gender and baseline BMI (27–34.9 and ≥ 35) within each site. Clinic staff involved in collecting data were blinded to participant assignment. Once group assignment was determined, non-clinic staff informed the participant and provided appropriate information about upcoming study activities. Intervention participants were notified when the group intervention was expected to begin; usual care participants were scheduled for the first follow up assessment, e.g. after 6 months. Usual care participants had no other obligation to the study and were free to initiate any weight loss effort on their own. We assessed all self-reported weight loss efforts at each follow-up for both the intervention and usual care participants.

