STRIDE began with a 6-month intensive group counseling phase followed by a less-intensive 6-month maintenance phase that included both group and individual contacts. Throughout both phases, implementation strategies included: frequent contacts, participant-centered group and individual facilitation approaches, and individual contacts that tailored the intervention to the participant’s preferences (as components of group meetings and separately, when needed). The program also targeted participants’ readiness to change, and encouraged group interactions that facilitated problem solving and social support, provided support for appropriate goal setting, and facilitated the acquisition of new information and skills for behavior change. Group leaders presented examples of behavioral options and used decisional balance approaches [41] to assist participants in moving toward action and setting new behavioral goals, paying careful attention to the cultural appropriateness of the program for minority participants. Sessions were designed to actively engage participants in small-group activities that fostered program ownership and allowed individual interaction with other participants and facilitators. Groups were co-led by two facilitators with complementary backgrounds; one with training as a mental health counselor, the other with training in nutritional interventions, though not a registered dietician. Having two interventionists provided flexibility during group sessions, however, and their differing backgrounds provided knowledge for managing a full range of problems and questions. All interventionists attended an initial two-day training meeting on the general intervention approach, and an additional two-day training meeting in the use of motivational interviewing techniques. In Year 1, an additional one-day training (webcast) addressed methods for presenting materials to individuals with mental illness, including those with cognitive and literacy limitations. Follow-up one-day trainings were held for all interventionists every six months. Trainers also provided ongoing supervision and individual training of all interventionists.

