#### Intensive intervention (Phase 1)

The core of the intervention program was a series of weekly group meetings designed to achieve a weight loss of 4.5-6.8 kg (10–15 pounds) over a 6 month period. Groups were two hours in length and included 20 minutes of physical activity (walking). Participants received a STRIDE workbook with details on program content, self-assessments and goal-setting procedures, booklets for self-monitoring of food and activity, cooking and meal planning guides with recipes, a copy of the Calorie King book [42] to help them learn about the calorie content of typical foods, and a resistance band for strength training. Ancillary materials can be downloaded at the study website [43].

Using a manualized protocol, facilitators promoted the following specific strategies for achieving changes in behavior, activity level, and weight: 1) self-monitoring of diet and physical activity, 2) developing personalized diet and physical activity plans, 3) moderately reducing calories, 4) reducing portion sizes, substituting alternative foods, and modifying meals so that they are lower in calories and fat, 5) focusing on fruits and vegetables and increasing low-fat dairy products and fiber intake (DASH diet [44]), 6) increasing physical activity, 7) identifying situations that trigger poor diet or physical activity choices, and developing and rehearsing specific plans of action to deal with those situations, and 8) graphing behavioral progress and individual weight change.

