#### Implementation and process evaluations

The implementation evaluation included observations of organizational and other facilitators and barriers to implementation; results of this evaluation are described elsewhere [25]. Fidelity assessments documented adherence to the intervention protocol and thus will allow examination of implementation differences across groups. Assessment of intervention fidelity includes both qualitative and quantitative measures.

The study design also included a process evaluation component, which sought to understand participants’ feelings toward, and responses to, the different elements of the intervention and to lifestyle change more generally. Semi-structured interviews lasting approximately 30 minutes were conducted with participants at 3- (n = 38), 9- (n = 35), and 18-months (n = 29) following randomization. Interviewers asked about barriers and facilitators of dietary and exercise changes. Of these, 76% (n = 78) were conducted with intervention participants and 24% (n = 24) with control participants. Interviews were transcribed verbatim and coded using Atlas.ti. Analyses will identify themes related to lifestyle improvements across participants; check coding will assess inter-coder reliability.

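### The intervention is delivered in groups, but neither the models nor the power calculation allow for correlation between group members; if there is any, standard errors are too small and type I error exceeds 5%

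*Protocol article*

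**What the plan says.** **Design.** Randomisation is by individual: "They were then randomized to either intervention or usual care groups using a blocked, stratified procedure" (Recruitment, screening, and randomization). In the intervention arm, "The core of the intervention program was a series of weekly group meetings" (Intensive intervention, Phase 1), followed by a monthly group meeting and a monthly individual contact in Phase 2. The section Tailored lifestyle intervention adds "Groups were co-led by two facilitators with complementary backgrounds", and says that the programme "encouraged group interactions that facilitated problem solving and social support". The other arm has no such structure: "Usual care participants had no other obligation to the study".

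**Analysis.** Under Effectiveness analyses of primary aims, the GEE is described as "accounting for the correlation among observations as a result of having multiple measures from the same person over time", and "the working covariance matrix will be specified as exchangeable". An unstructured matrix is one of the sensitivity analyses. Age, site and outcome-related medication are covariates. The ANCOVA and logistic regression for the additional weight outcomes adjust for age, site and weight-related medication. The power section uses repeated measures ANOVA with an allowance for attrition only. None of these sections mentions treatment group or facilitator as a source of correlation.

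**The concern.** Members of one treatment group share two facilitators, a meeting place, a calendar period and one another's support, which the programme sets out to encourage. Any of these can make their weight and laboratory changes resemble each other. The mean of the intervention arm then carries less information than the same number of independent people would give.

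Both working matrices in the plan describe visits within a person. Whether the standard errors are model-based or robust (the article does not say which), with the person as the cluster they treat two members of the same group as independent. The site covariate takes out at most differences between sites, not differences between groups at one site. For any positive correlation the error runs one way: intervals too narrow, p-values too small, planned power too high.

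**Working it through.** **Inputs from the article.** Planned total 280; attrition 10%, 15% and 20% at 6, 12 and 24 months; alpha .05; differences in percentage weight change of 5.9 − 1.6 = 4.3, 4.4 − 1.6 = 2.8 and 3.6 − 1.8 = 1.8 points; stated power .96, .87 and .80; 200 randomised.

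**Assumptions, because the article gives no figure.** Members per group m = 8 to 15; ICC ρ = 0 to 0.10 in the intervention arm; equal allocation; equal group sizes; equal outcome variance in both arms; two-sided tests.

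**1. The stated power.** It cannot be reproduced, since no SD is given. With n per arm of 126, 119 and 112 and a two-sample normal approximation, SD = difference / [(1.96 + z_power) × √(2/n)]. The stated powers then imply SDs of 9.2, 7.0 and 4.8 percentage points, with no room for a design effect.

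**2. Standard error and type I error.** Only one arm is clustered:

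- intervention-arm design effect: DE = 1 + (m − 1)ρ
- true variance / person-level variance of the difference: R = (1 + DE)/2
- shortfall of the reported SE: 1 − 1/√R
- actual type I error: 2 × [1 − Φ(1.96/√R)]

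For m = 12 and ρ = 0.05: DE = 1.55, R = 1.275, √R = 1.129. The shortfall is 1 − 1/1.129 = 11%, and the type I error is 2 × [1 − Φ(1.736)] = 8.3%.

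| m | ρ | R | √R | Reported SE too small by | Type I error, formula | Type I error, simulated |
|---|---|---|---|---|---|---|
| 10 | 0 | 1.000 | 1.000 | 0% | 5.0% | 5.0% |
| 10 | 0.01 | 1.045 | 1.022 | 2% | 5.5% | 5.6% |
| 8 | 0.02 | 1.070 | 1.034 | 3% | 5.8% | 6.2% |
| 10 | 0.05 | 1.225 | 1.107 | 10% | 7.7% | 7.8% |
| 12 | 0.05 | 1.275 | 1.129 | 11% | 8.3% | not run |
| 15 | 0.05 | 1.350 | 1.162 | 14% | 9.2% | 9.3% |
| 15 | 0.10 | 1.700 | 1.304 | 23% | 13.3% | 13.1% |

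The simulations used 100 per arm, a test with person-level variance and 20,000 replicates per setting. A small GEE simulation with an exchangeable working matrix (m = 10, 500 replicates per setting) rejected in 5.2%, 8.2% and 7.4% of trials at ρ = 0, 0.02 and 0.05. With Monte Carlo error of about one point or more, it supports the direction but not the exact size.

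**3. Power.** Power = Φ[(1.96 + z_power)/√R − 1.96], using the SDs from step 1. For m = 10 and ρ = 0.05:

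- 6 months: 3.711/1.107 − 1.96 = 1.39, power .92 (stated .96)
- 12 months: 3.086/1.107 − 1.96 = 0.83, power .80 (stated .87)
- 24 months: 2.802/1.107 − 1.96 = 0.57, power .72 (stated .80)

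With 200 randomised instead of 280, the same SDs give .88, .74 and .66 without clustering, and .81, .65 and .57 with it.

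**The case against.** **The size is unknown.** The article reports no ICC, number of groups or group size. At an ICC of 0 there is no inflation, and at 0.01 with 10 per group the test runs at 5.5%, which few would worry about. Clustering in one arm only also halves the variance inflation. This stands. A reader might infer that every primary comparison certainly has error bars that are too narrow; the documents support that only if outcomes correlate within groups.

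**Group contact is limited.** Goals are set individually, make-up sessions were offered, Phase 2 has one group meeting a month, and fixed group membership is not stated. The 24-month visit falls about a year after group contact ends. This stands too: one ICC need not fit all time points, and the effect may be smaller at 24 months.

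**The implementation section.** It says "Fidelity assessments documented adherence to the intervention protocol and thus will allow examination of implementation differences across groups". A reader might take this as the plan predicting that groups will differ. It says only that differences can be examined, and it concerns adherence to the protocol, not correlation of outcomes.

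**The article is condensed.** A full protocol or analysis plan might address grouping. This carries less weight. The article fixes the source of correlation, distribution, link, working matrix, covariates and a list of sensitivity analyses for every outcome, and none of them reaches the treatment group.

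**The remedy is imperfect.** With about 7 to 13 clusters, sandwich variances are unstable even when corrected. That is a reason for a small-sample method, or for placing the model among the sensitivity analyses. It does not justify treating group members as independent.

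**Conclusion.** The point holds in conditional form. The design is partially nested, and the GEE, the ANCOVA, the logistic regression and the power calculation all leave out correlation between members of a treatment group. That much rests on the article's own text. The consequence rests on a positive within-group ICC, which shared facilitators and encouraged peer support make plausible but which the article does not quantify.

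Over the assumed range, the reported standard error is 0 to 23% too small and the nominal 5% test runs at 5% to about 13%. At the upper end the true standard error is 30% larger than the reported one. A reader might restate that as a reported standard error 30% too small, but the shortfall is 1 − 1/1.304 = 23%.

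This should be corrected, but it does not by itself invalidate the trial. The omission is clear; its size is uncertain until the group structure is known.

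**What to change.** State the number and size of the treatment groups and how membership was defined, including for make-up sessions. Then fit a partially nested model in one of two ways:

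- a mixed model with a random effect for treatment group in the intervention arm only, allowing that effect to act on change over time, plus person-level covariance; or
- GEE clustered on treatment group, with each usual-care participant as a cluster of one and a small-sample-corrected variance and degrees of freedom.

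Treat the ANCOVA and logistic models in the same way. At minimum, add this analysis to the pre-specified sensitivity analyses for every primary outcome and report the estimated within-group ICC. When power is restated, apply a design effect with its assumed m and ICC written out.

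**Cost.** No new participant measurements are needed, but group membership must be retrieved from delivery records; the article does not say that it was recorded. Intervals will widen, possibly materially. With about 100 intervention participants (equal allocation assumed) there would be only about 100/15 ≈ 7 to 100/8 ≈ 13 groups, so the degrees-of-freedom correction adds to the widening. If the ICC is near zero the estimates will change little, but that correction will still cost some precision.

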### Assessment data collection and measurement

Intervention and usual care groups were assessed at baseline, 6, 12, and 24 months. Laboratory, physiological and anthropometric measures were obtained at each assessment and included: 1) height in meters measured to the nearest 0.1 cm (baseline only), 2) weight in kilograms measured to the nearest 0.1 kg (body mass index was calculated as the Quetelet index [kg/m^2^]), 3) waist circumference, measured over participants’ underwear using inelastic tape at the narrowest part of torso and measured in a horizontal plane without compressing the skin, and 4) blood pressure, measured while participants were seated with legs uncrossed and without talking after a 5-minute rest period, and then again after an additional 30 second rest period. Blood was drawn and all lab panels were collected after an overnight (8–12 hour) fast. Tests included: 5) fasting insulin, 6) fasting plasma glucose, 7) fasting triglycerides, and 8) fasting cholesterol (total, HDL, LDL).

We followed the National Cholesterol Education Program (NCEP) guidelines [45] and defined metabolic syndrome as: Individuals with 3 or more of the following risk factors: a) waist circumference greater than 102 centimeters in men or 88 centimeters in women; b) triglycerides plasma level of 150 mg/dL or greater; c) HDL-cholesterol plasma level less than 40 mg/dL for men or less than 50 mg/dL for women (or taking cholesterol-lowering medications); d) blood pressure of 130/85 mm Hg or greater (or taking antihypertensive medications), and/or e) fasting glucose greater than or equal to 110 mg/dL (or taking glucose lowering medications).

To assess insulin resistance, we calculated the Homeostasis Model Assessment Index for Insulin Resistance (HOMA-IR) as follows: fasting glucose [mmol/L] × fasting insulin [μU/mL]/22.5. This index correlates very highly with the gold standard hyperinsulinemic euglycemic clamp [46].

We included several self-reported measures to describe participants and assess health and functional status and medication use. These measures are shown in Table 1.

**Table 1 T1:** STRIDE measures and data collection schedule

	**BL**	**6 month**	**12 month**	**24 month**

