#### Power analysis of primary aims

We used data from PREMIER DASH diet arm results [30] to estimate power for repeated measures analysis of variance for change in weight. We used repeated measures ANOVA given the lack of well-established methods for estimating power using GEE. Data were available for change at 6 and 18 months. Because reported means and standard deviations were based on completers alone, we adjusted for attrition in our power analyses (although primary analyses will be intent-to-treat). PREMIER reported a 5.9% decrease in weight at 6 months for the DASH diet group and a 1.6% decrease for control (advice only). With an initial total sample size of 280, a 10% (worst case) attrition rate at six months, and alpha level of .05, we have power of .96 to detect a significant group-by-time interaction at 6 months. Using the 18-month values (−1.6% for advice only, -4.4% for DASH) as a conservative estimate for weight change at 12 months, we have power of .87 for the group-by-time interaction term for weight (assuming a 15% worst-case attrition rate). To estimate power at 24 months, we assumed the same rate of weight gain in the DASH group and weight loss from 6 to 18 months in the UC group, consistent with PREMIER. For a 3.6% decrease from baseline in the DASH group and 1.8% decrease for UC at 24 months, we have power of .80 to detect a significant group-by-time interaction at 24 months, assuming 20% attrition. Power for waist circumference, fasting insulin, and insulin sensitivity were based on data reported by Ard [31]. Power for total cholesterol, LDL, and HDL were based on data reported by Obarzanek [64]. Only baseline and 6-month means were available for these variables, so we have computed power to detect a significant group-by-time interaction at 6 months only. For all variables, power exceeds .95 to detect the group-by-time interaction.

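### Age and site, read as main effects, leave the primary time-by-group estimate practically unadjusted; they should enter with visit interactions

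*Protocol article*

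**What the plan says.** All references are to the protocol article.

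- *Effectiveness analyses of primary aims*, target: "The primary coefficient of interest will be the time by group (control vs. intervention) interaction".
- Same section, baseline covariates: "We will include age and study site and time-invariant covariates". The second *and* is probably a slip for *as*. No covariate-by-time term is mentioned.
- Same section, other covariates: "Use of outcomes-related medications will be included as time-varying covariates".
- Same section, model: "The GEE models will be based on the normal distribution with identity link, and the working covariance matrix will be specified as exchangeable".
- Same section, missing data: participants with incomplete follow-up are kept, under a missing-at-random assumption.
- *Assessment data collection and measurement*: "Intervention and usual care groups were assessed at baseline, 6, 12, and 24 months". Baseline is therefore one of the repeated responses.
- *Recruitment, screening, and randomization*: blocked, stratified allocation so that "group assignments remained balanced across gender and baseline BMI (27–34.9 and ≥ 35) within each site".

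**The concern.** The primary coefficient is a difference between arms in change from baseline. A covariate that is constant within a person and has no interaction with time adds the same amount to the baseline and follow-up values, so it cancels from every change. Age and site would then explain differences in level between people, which the contrast does not use. They would explain nothing about differences in change.

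Two things follow.

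1. **Description.** The primary result would be called adjusted for age and site when it is practically the unadjusted one. Later in the same section, age and site also enter an ANCOVA of percentage weight change and a logistic model. The outcome there is already a change, so they do adjust. The same covariate list has different force in the primary and supporting weight analyses.
2. **Precision.** Allocation was stratified within sites that serve different populations: two community mental health centres and an integrated health system. If mean change differs by site, that variation stays in the residual and the reported SE is wider than it need be. Precision is not plentiful, since power was computed for 280 and 200 were randomised.

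**Working it through.** **Plan's own figure.** The article gives none for the effect of covariate adjustment. Its power statements quote no SD, so they cannot be reproduced, and nothing below rests on them.

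**Step 1: algebra.** Let person *i* at visit *k* have mean μ_k + α·g_i + β_k·g_i + γ'x_i. Here g is arm, x holds age and site, and β_0 = 0. Then

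Y_ik − Y_i0 = (μ_k − μ_0) + β_k·g_i + error,

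and γ'x_i has gone. With complete data, an exchangeable working matrix and an identity link, the GEE splits into a part for person means and a part for deviations from those means. Age and site appear only in the first and β_k is determined by the second. The estimate is the difference between arms in mean change, with or without x, and the same holds for its robust SE.

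**Step 2: does the plan break the cancellation?** Incomplete visits and time-varying medications both do. GEE fits to simulated data compared models with and without age and site main effects (n = 200; visits at 0, 6, 12 and 24 months; 120 data sets per scenario). Attrition of 10/15/20% is from *Power analysis of primary aims*. The within-person correlation of about .95 for weight, the site effects and the dropout model are assumptions.

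| Scenario (weight) | Largest shift in estimate | Largest shift in SE |
|---|---|---|
| Complete, no medication term | 0 | 0 |
| Complete, medication term | 0.018 kg | 0.002 kg |
| Attrition 10/15/20% | 0.043 kg | 0.003 kg |
| Attrition, medication and site differences in change | 0.077 kg | 0.005 kg |

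The SE in the last row is about 1.1 kg, so the largest shift is 0.077/1.1 = 0.07 SE. The mean shift is under 0.01 kg.

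For a standardised outcome with attrition (24-month term), the shift averages 0.02 SE (largest 0.09) at correlation .95. At correlation .5 it averages 0.05 to 0.06 SE (largest 0.23). The SE changes by at most 1.2%.

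**Step 3: cost in precision.** If sites differ in mean change with between-site variance B and within-site variance W, the SE ratio without and with site-by-visit terms is about √(1 + B/W). Assume a within-site SD of change of 9 kg (W = 81) and a 50/25/25 site split. For a gap *g* between extreme sites, B is at most g²/4:

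- g = 2: √(1 + 1/81) = 1.006
- g = 4: √(1 + 4/81) = 1.024
- g = 6: √(1 + 9/81) = 1.054

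Simulation under the same assumptions (180 analysed, allocation stratified by site, 6,000 trials per gap) also included a small age effect. It gave 0.5%, 2.8% and 6.5%, which agrees to about one percentage point. In sample-size terms: 1.005² = 1.01, 1.028² = 1.06 and 1.065² = 1.13, or about 1%, 6% and 13%.

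In the 6 kg case, type I error was 4.2%, and power for a 3 kg effect was .58 rather than .61. The .61 checks by hand: SE = 2×9/√180 = 1.342, 3/1.342 = 2.236, and Φ(2.236 − 1.960) = .61.

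**Step 4: second check.** In the Step 2 simulations with complete data and assumed mean site changes of −3, 0 and +3 kg, the mean SE at 6 months was 1.048 kg with main effects and 0.986 kg with visit interactions. The ratio is 1.063 and the variance ratio 1.13. With no site difference the SEs were 0.992 and 0.986 kg, a 0.6% difference. The estimate barely moved (−4.500 and −4.481 kg in the site-difference case).

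**The case against.** **Main-effects entry is inferred.** No formula is printed, the sentence is garbled, and *time-invariant* describes the variables, not how they enter. An article may leave model terms to a fuller plan. This stands as a limit on certainty. Even so, the section fixes family, link, working matrix, covariates and target coefficient, and names exactly one interaction, so main effects are the natural reading.

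**A reader might infer that the adjustment cannot change the result at all.** That is true only with complete data and no time-varying covariate, and the plan has both incomplete data and medication terms. The shifts are tiny for weight. They can be larger for outcomes less correlated over time; insulin and cholesterol are also primary aims, and the article gives no within-person correlations for them. Covariates related to dropout can also help the stated missing-at-random assumption, so listing age and site is not pointless.

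**A reader might infer that ignoring the site strata makes the inference invalid.** The document does not support that. Site is in the model, and the only error found is on the cautious side (type I error 4.2% in the largest case).

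**The cost rests on assumed site gaps.** This also stands. A 6 kg gap between sites in mean change is large beside the intervention's own 6-month target of 4.5 to 6.8 kg, and at 2 kg the SE is only 0.5% too wide.

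**Conclusion.** The point holds as a cheap improvement, not as a threat to validity. Read as main effects, age and site cancel exactly from the time-by-group contrast in the ideal case. Under the planned attrition and medication terms they cancel almost entirely for weight. Calling the primary result adjusted for age and site would then mislead.

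The price is an SE that is conservatively wide by roughly 0.5% to 6.5% if site means of change differ by 2 to 6 kg. That range assumes a 9 kg within-site SD, a 50/25/25 site split and a small age effect, none of which the article supplies. A smaller SD of change would make a given gap cost more, and a larger one less. If change does not differ by site, almost nothing is lost.

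**What to change.** Correct the sentence in *Effectiveness analyses of primary aims* along these lines: age and study site will be included as covariates, each with its interaction with visit. Use the same form for any other stratification factor added. Gender and BMI class are not in the list now, and as main effects they would add almost nothing to the time-by-group test.

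Cost: age (1) plus site (2 indicators), times three follow-up visits, is up to 3 × 3 = 9 extra parameters per outcome in 200 participants. The change uses data already collected. The gain is small if change does not depend on site or age.

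Fitting follow-up visits alone with main effects is not a substitute. The covariates would still cancel from time by group, and baseline weight would be left out. With a baseline SD of 25.1 kg against the assumed 9 kg for change, comparing unadjusted follow-up weights would give an SE roughly 25.1/9 = 2.8 times as large.
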